**Fig. 5 Fig5:**
[figure not shown]
Sampling strategy

### Data collection methods

Data will be collected both retrospectively (for the baseline measurement) and prospectively, from three different sources: the CBOs, the SFH state-level offices, and the SFH headquarters (Fig. 3).

For retrospective data collection, CBO managers from both treatment and control groups were asked to bring all CBO records with them to the Abuja training, and to utilize their records to input data on staff salaries, supplies, clients served, rent, utilities, and trainings at their CBO for records dated between January 2016 to July 2017. Questionnaires were built from those used previously in the ORPHEA study [16]. All participants were also asked to complete a questionnaire on management practices and job satisfaction.

For prospective data collection, training participants will collect data from their own CBO on monthly inputs (salaries, commodities, rent, utilities, and trainings), outputs (FSW served, by intervention) and management practices on their tablet with the installed survey software. Each month, participants will do this independently, but research assistants and the field data manager will review the data remotely and ask for clarification from the sites as needed. Additionally, research assistants will conduct in-person monitoring at the beginning of the prospective data collection period. The purpose of the monitoring visits will be to correct data issues and support the CBO participants on the technical aspects of tablet use as needed.

### Data management

All questionnaires will be administered using Qualtrics Survey Software [13]. Data will be downloaded as csv files and imported into STATA [17] for cleaning and analysis.

### Statistical methods

At the time of writing, baseline data cleaning was in process. Findings from both the baseline data and prospective data collection will be published in subsequent papers. For the purposes of baseline analysis, the data will be restricted to the 2016 fiscal year (January to December).

For the endline analysis, we will first assess baseline balance between treatment and control groups on key process and outcome measures, including inputs, outputs, costs and cost per FSW served. We will also examine descriptive statistics of the management scores. We will calculate unit costs and then measure the mean cost per client served at baseline and at endline for treatment and control groups. We will compare the two through multivariate ordinary least squares (OLS) regression analysis, using a “difference-in differences” (DiD) approach [18] to account for time-invariant differences between treatment and control groups:2$${\hbox{Y}}_{\text{ic}} = {\hbox{a}} + {\hbox{b}}_{ 1} {\hbox{x}}_{ 1} + {\hbox{b}}_{ 2} {\hbox{x}}_{2} + {\hbox{b}}_{ 3} ({\hbox{x}}_{1*} {\hbox{x}}_{2}) + [{\hbox{b}}_{4} {\hbox{x}}_{4} + \ldots {\hbox{b}}_{\text{n}} {\hbox{x}}_{\text{n}} ] + {\hbox{e}}$$where the outcome Y is the mean cost per client served for each intervention *i*, in CBO *c* x_1_ is the treatment assignment (x_1_ = 1 if treatment and x_1_ = 0 if control); x_2_ is the time point (x_2_ = 0 if before and x_2_ = 1 if after the intervention); x_4 _− x_n_ are all variables that were identified as imbalanced at baseline. Despite the rigorous randomization procedure, the small sample size and diversity in the country may still cause unobservable characteristics linked to the implementation of services—and more importantly, to efficiency—to be unbalanced between treatment and control groups. In anticipation of this possibility, using a quasi-experimental DiD approach allows any baseline differences to be “differenced out” when measuring the effect.

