**Methods:**

The present protocol describes the design of a cluster-randomized control trial to estimate the effect of management practices on efficiency. Specifically, we will evaluate the impact of an intervention focused on improving management practices among community-based organizations (CBOs), on the costs of HIV prevention services for female sex workers (FSW) in Nigeria. To design the intervention, we used a qualitative, design thinking-informed methodology that allowed us to understand management in its organizational context better and to develop a user-centered solution. After designing the suite of management tools, we randomly assigned 16 CBOs to the intervention group, and 15 CBOs to the control group. The intervention consisted of a comprehensive management training and a management “toolkit” to support better planning and organization of their work and better communication between CBOs and community volunteers. Both treatment and control groups received training to record data on efficiency—inputs used, and outputs produced. Both groups will be prospectively followed through to the end of the study, at which point we will compare the average unit cost per FSW served between the two groups using a quasi-experimental “difference-in-differences” (DiD) strategy. This approach identifies the effect of the intervention by examining differences between treatment and control groups, before and after the intervention thus accounting for time-constant differences between groups. Despite the rigorous randomization procedure, the small sample size and diversity in the country may still cause unobservable characteristics linked to efficiency to unbalanced between treatment and control groups at baseline. In anticipation of this possibility, using the quasi-experimental DiD approach allows any baseline differences to be “differenced out” when measuring the effect.

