### Trial design

This study is a cluster-randomized control trial (C-RCT) that examines the role of management practices on the costs of HIV services for FSWs in Nigeria. The project consists of two phases: (1) a design phase that uses qualitative methods to define and understand study population needs, and (2) an experimental phase, that implements a C-RCT. The design phase informed the content of a management intervention that will be implemented in CBOs and evaluated throughout the experimental phase.

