### Allocation

Thirty-two sites were stratified in two strata of geographic region—north and south—with 8 sites in the north stratum and 22 sites in the south stratum. The north and south regions are climatically, linguistically and culturally distinct. More importantly, the HIV epidemic also affects the regions differently; the largest concentration of HIV/AIDS is in the south. Given that such factors are likely not independent of HIV service delivery and efficiency, stratifying the randomization by these strata improves the balance between treatment groups. Within strata, we randomly assigned sites to either treatment or control groups. Treatment status was assigned using the randomization package in STATA [17]. We specified that the package run 10,000 iterations and selected the randomization with the highest (i.e. least significant) p-values across t-tests on four key input and output indicators (clients served, referrals given, condoms distributed, and number of FSW tested). We allocated 16 sites to the treatment group and 16 to the control group. One site was later excluded because it no longer served the FSW population at the start of the trial period. The final sample included 31 sites, with 16 in the treatment group and 15 in the control group (Fig. 5). We explained to participants that they were involved in a costing study, but we never revealed whether they were part of the treatment or the control groups.

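### Equation 2 pools before and after values of the same 31 CBOs in OLS with no CBO term, so its conventional standard error for the effect is too large

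*Protocol article*

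**What the plan says.** The Statistical methods section of the protocol article sets out the endline analysis. The authors write: "We will calculate unit costs and then measure the mean cost per client served at baseline and at endline for treatment and control groups". They then state: "We will compare the two through multivariate ordinary least squares (OLS) regression analysis", in a difference-in-differences form given as Equation 2.

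The terms of Equation 2 are these:

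- **Outcome:** "the outcome Y is the mean cost per client served for each intervention", indexed by service and CBO.
- **x1:** an indicator of treatment or control arm.
- **x2:** "is the time point (x_2_ = 0 if before and x_2_ = 1 if after the intervention").
- **b3:** the coefficient of x1 times x2, which is the treatment effect.
- **x4 to xn:** these "are all variables that were identified as imbalanced at baseline".
- **e:** a single residual.

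The same organizations supply both time points. The abstract says: "Both groups will be prospectively followed through to the end of the study". The Allocation section says: "The final sample included 31 sites, with 16 in the treatment group and 15 in the control group". The article mentions no CBO fixed or random effect, no differencing within CBO and no clustered variance.

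**The concern.** Equation 2 has a term for the arm but none for the CBO. The coefficient b1 takes out the difference between the two arm means. Lasting differences between CBOs within an arm stay in e, so the before and after residuals of one CBO are correlated. Unit costs of one organization, with continuing staff, premises and service area, are unlikely to be uncorrelated from one year to the next.

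Conventional OLS assumes that correlation is zero. It therefore charges b3 with between-CBO variation that in fact cancels when each CBO is compared with itself. The section justifies difference-in-differences by the removal of baseline differences between groups. That argument supports the point estimate and says nothing about its standard error.

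At stake are intervals wider than the data warrant and a real effect on unit cost reported as inconclusive. With 31 CBOs, and with the Discussion already expecting wide standard errors, the trial has little precision to lose.

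**Working it through.** **Inputs from the article.** 16 treatment and 15 control CBOs (Allocation); two time points and the terms of Equation 2 (Statistical methods); 80% power for a difference of 1.09 in log cost with 32 sites (Sample size).

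**Inputs assumed.** The within-CBO before-after correlation r, the SD, a two-sided alpha of 0.05, and no covariates. The article gives none of these values.

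**1. The plan's own figure.** The 1.09 cannot be reproduced, because no SD, alpha or sidedness is stated. Solving backwards for 16 + 16 sites, with the normal approximation:

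SD = 1.09 / [(1.960 + 0.842) × sqrt(1/16 + 1/16)] = 1.09 / 0.991 = 1.10.

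The noncentral t version gives 1.065. With 16 + 15 the two values are 1.08 and 1.05.

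**2. Variance of b3.** For one service there are 31 × 2 = 62 rows, and 62 - 4 = 58 residual degrees of freedom.

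- Assumed by conventional OLS: 2 × SD² × (1/16 + 1/15)
- True: 2 × SD² × (1 - r) × (1/16 + 1/15)
- Ratio of standard errors: 1/sqrt(1 - r), whatever the SD

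With SD 1.065, the OLS value is sqrt(2 × 1.134 × 0.1292) = 0.541 at every r.

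| r | True SE | OLS SE / true SE |
|---|---|---|
| 0.3 | 0.453 | 1.20 |
| 0.5 | 0.383 | 1.41 |
| 0.7 | 0.296 | 1.83 |

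**3. Error rate and power.** Simulation with 16 and 15 CBOs and a true difference of 1.09, comparing pooled OLS (58 df) with an analysis of CBO changes (29 df):

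| SD, runs per cell | r | Type I error, OLS | Power, OLS | Power, changes |
|---|---|---|---|---|
| 1.065; 4,000 | 0.3 | 2.2% | 51% | 64% |
| 1.065; 4,000 | 0.5 | 0.7% | 51% | 78% |
| 1.065; 4,000 | 0.7 | 0.0% | 52% | 94% |
| 1.10; 20,000 | 0.3 | 2.0% | 48% | 62% |
| 1.10; 20,000 | 0.5 | 0.6% | 49% | 76% |
| 1.10; 20,000 | 0.7 | 0.1% | 48% | 93% |

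The analysis of changes kept its type I error between 4.5% and 5.5%. OLS power stays near one half at every r for a simple reason: the estimate must exceed about 2.00 × 0.541 = 1.08 to be significant, and the true difference is 1.09.

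**4. Covariates.** If baseline covariates explain a share q of the total variance, all of it between CBOs, the ratio becomes about sqrt((1 - q)/(1 - r)). At r = 0.5 and an assumed q = 0.2 that is sqrt(0.8/0.5) = 1.26 in place of 1.41. The discrepancy shrinks but does not vanish while q is below r. Covariates fixed over time leave b3 unchanged in a balanced panel.

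**5. Several rows per CBO and period.** If rows were stacked, the result would depend on shocks shared by all rows of one CBO in one period. Variance shares are assumed:

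| Rows stacked | CBO share | CBO-by-period share | Type I error, OLS |
|---|---|---|---|
| 3 services | 0.5 | 0 | 0.7% |
| 3 services | 0.5 | 0.1 | 2.7% |
| 3 services | 0.5 | 0.3 | 6.8% |
| 3 services | 0.2 | 0.5 | 14.8% |
| 12 months | 0.5 | 0 | 0.9% |
| 12 months | 0.5 | 0.05 | 6.8% |
| 12 months | 0.5 | 0.20 | 24.6% |

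**The case against.** The strongest reply is that Equation 2 fixes the mean model and the OLS estimator but not the variance estimator. A bare e does not assert independence, and OLS with standard errors clustered by CBO has exactly these regressors. A condensed article may leave that choice to an analysis plan that is not shown. This stands in part: nobody can say that the trial will report a wrong standard error. It does not dispose of the point. The article lists its model terms and includes no CBO effect, and followed as written with conventional standard errors it gives a worse test than simple alternatives using the same data.

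A reader might infer three stronger things that the documents do not support.

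- **Excess false positives.** On the natural reading, one before and one after value per CBO and service, the type I error falls below 5%.
- **Anti-conservative results from stacked rows.** Positive correlation among rows is not enough, because a time-constant CBO effect cancels from b3. The direction turns on the CBO-by-period shocks. The text also does not say that monthly rows enter Equation 2; the Unit cost section defines an annual average.
- **Power of about 51% as a property of this trial.** Equation 2 uses mean cost without a log, the 1.09 belongs to log cost per client tested positive, the SD is back-solved, r is assumed, and covariates are left out of the simulation.

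**Conclusion.** The concern holds in this form. Equation 2 makes no provision for repeated measurement of the same CBO. With two rows per CBO and service, the conventional OLS standard error of b3 is right only at r = 0, and at positive r it is too large by about 1/sqrt(1 - r). That factor does not depend on the SD or the effect size. It does assume a balanced panel, equal variance at both time points and no covariates.

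The harm is lost power and over-wide intervals, not bias and not false positives. The size depends on r, which the article does not give; over r from 0.3 to 0.7 the inflation runs from 1.20 to 1.83. The power figures only illustrate what that inflation can cost.

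**What to change.** For each service, replace Equation 2 by an analysis with one row per CBO: endline unit cost on arm and baseline unit cost, or the CBO change score on arm. Equivalently to the change score, add CBO fixed effects to Equation 2; b1 and any time-constant covariates then drop out.

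If the pooled OLS form is kept, state that standard errors are clustered by CBO, with a small-sample correction because there are only 31 clusters. Bias-reduced cluster variance with Satterthwaite degrees of freedom, or a wild cluster bootstrap, would serve. State also that each CBO contributes one before and one after value per service, so that the row structure is not left open.

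The cost is a change of wording and a line or so of analysis code, best made before endline data are analysed. No new data are needed.

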### Sample size

Since we had a fixed number of sites (n = 32), we ran power calculations to examine the varying amounts of power that were achievable, given a variety of effect differences between treatment and control groups. The point estimate for log cost per client tested positive and accompanying standard error used in the calculations are based on data from a relevant previous costing study (ORPHEA: Assessing cost and technical efficiency of HIV prevention interventions in sub-Saharan Africa) [14–16]. Given sample size and assumptions, there was 80% power to detect a 1.09 unit difference (USD) in the log cost between the treatment and control groups.

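### The stated 80% power is for log cost per client tested positive, but Equation (2) analyses untransformed cost per client served, so the power figure does not belong to the planned analysis

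*Protocol article*

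**What the plan says.** Sample size (Protocol article) starts from 32 available sites: "Since we had a fixed number of sites (n = 32), we ran power calculations". The input is "The point estimate for log cost per client tested positive and accompanying standard error used in the calculations", taken from an earlier costing study, and the result is that "there was 80% power to detect a 1.09 unit difference (USD) in the log cost between the treatment and control groups". The SD, the significance level and the sidedness are not printed.

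Outcomes and Unit cost define the primary outcome as total cost divided by number of clients, for each of three services, with no transformation. Statistical methods fits Equation (2) by ordinary least squares, "where the outcome Y is the mean cost per client served for each intervention". The effect is b3, the treatment-by-time interaction. No logarithm, log link or ratio is mentioned for the analysis. The same section expects that baseline imbalance may occur in a small sample and gives this as the reason for DiD.

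Allocation reports that "The final sample included 31 sites, with 16 in the treatment group and 15 in the control group".

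**The concern.** The power statement and the model equation differ in two ways.

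- **Scale.** Power concerns a difference of logs, which is a ratio of costs. In Equation (2), b3 is an additive difference in cost.
- **Denominator.** Power concerns cost per client tested positive. Equation (2) concerns cost per client served.

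The power statement therefore does not tell the reader what the planned analysis can detect. If unit costs are strongly right-skewed, which the use of logs for power makes plausible, a few high-cost organisations out of 31 would dominate the raw means and power could be far below 80%.

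A second, smaller issue concerns the reason given for DiD. Additive differencing removes a baseline gap if both arms change by the same amount. If costs in both arms rise by the same percentage, the gap grows and the growth appears in b3.

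**Working it through.** **Inputs from the documents.** Detectable difference 1.09 on the log scale; power 80%; 32 sites, with "We allocated 16 sites to the treatment group and 16 to the control group"; final sample 16 v 15.

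**Assumptions.** Two-sided 5% significance; log-normal unit costs; the implied log SD carried over to cost per client served; a DiD test that compares within-organisation changes between arms. Before-after correlation ρ is not given and is varied.

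**Step 1: the plan's own figure.** With no SD or significance level printed, 1.09 cannot be reproduced independently. It can be solved for the SD it implies:

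difference = SD × √(1/n1 + 1/n2) × (z for 97.5% + z for 80%)

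For 16 v 16: SD = 1.09 / (√(1/16 + 1/16) × (1.960 + 0.842)) = 1.09 / (0.3536 × 2.802) = 1.10. With the t distribution the SD is 1.06. For 16 v 15 the values are 1.08 and 1.05. One-sided testing at 16 v 16 (normal) would give 1.24.

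**Step 2: what 1.09 means.** exp(−1.09) = 0.336, a 66% fall in cost; exp(1.09) = 2.97, nearly a threefold rise. The currency unit cancels in a difference of logs, so the figure has no USD unit. It has no fixed counterpart in b3 either, because the same ratio gives different cost differences at different baseline costs.

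**Step 3: raw-scale spread under log-normality.** Coefficient of variation = √(exp(SD²) − 1). At log SD 1.065 this is √(exp(1.134) − 1) = 1.45; at log SD 0.5 it is 0.53.

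**Step 4: power of DiD at the stated 1.09 reduction, 16 v 15.** On logs, the SD of a change is SD × √(2(1 − ρ)). At ρ = 0.5 it equals the SD itself, so log-scale DiD keeps about the power of an endline comparison, 79%. Simulated power:

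| Correlation ρ | Log SD 1.065, logs | Log SD 1.065, raw | Log SD 0.7, raw | Log SD 0.5, raw |
|---|---|---|---|---|
| 0.5 | 79% | 31% | 71% | 95% |
| 0.7 | 95% | 42% | 84% | 99% |
| 0.8 | 99% | 53% | 91% | 100% |
| 0.95 | 100% | 81% | 99% | 100% |

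Repeat runs differ by about one percentage point. At log SD 0.5 log-scale power is 100% throughout. An effect of 1.09 is then so large that both scales are near their ceiling.

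**Step 5: common price growth.** Let costs in both arms grow by the proportion g with no true effect. Then

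raw b3 = g × (baseline mean, treatment − baseline mean, control); log-scale b3 = 0.

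With g = 30% (assumed; the documents give no figure):

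- means 10 v 10: 0.3 × 0 = 0
- means 12 v 10: 0.3 × 2 = 0.6, or 6% of the control baseline
- means 15 v 10: 0.3 × 5 = 1.5

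Over repeated randomisations under the same growth and no effect, raw b3 averages about zero and the change-score test rejects in 3–5% of runs.

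**The case against.** Several stronger readings are tempting, and the case against them is sound.

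- **That raw-scale DiD turns common price growth into a false effect.** In general it does not. Step 5 shows no average bias and no type I inflation. The artefact needs both a realised baseline gap in unit cost and proportional growth, and the documents give neither figure. Choosing the allocation for balance on four input and output indicators may make a large gap less likely, though unit cost was not among them.
- **That unit cost is known to be skewed.** No section says so. The SD of about 1.06 is back-solved with an assumed significance level and belongs to another outcome from another study. Raw-scale power could equal or exceed 80% if the true log SD is smaller or the correlation is high.
- **That the log scale is the only right one.** Cost estimates are meant for national planning, for which an arithmetic mean difference is a legitimate target. Nor do logs cure every trend: if both arms rise by the same amount, 12 to 15 and 10 to 13, raw b3 is 0 but log-scale b3 is ln(15/12) − ln(13/10) = 0.223 − 0.262 = −0.039. A constant price set removes price growth on either scale.

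The mismatch itself survives all of this. It cannot be put down to detail left for an analysis plan, because the article prints both the power statement and the model equation, and they disagree.

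**Conclusion.** The point holds as a mismatch. The stated 80% power, for a cost ratio of 0.34 or 2.97 in cost per client tested positive, does not describe the stated analysis of raw cost per client served, and the USD label is wrong for a log difference. This part rests on the text alone.

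The size of the power loss is conditional. With log-normal costs and log SD about 1.06, raw-scale DiD has about 31–53% power at correlations of 0.5–0.8 and 81% at 0.95, against 79–100% on logs. At log SD 0.5 raw power is 95–100% and the loss is small. Which case applies to cost per client served cannot be told from the documents.

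The price-growth point is a limit on what additive differencing can do in a single trial with unequal baseline means, the situation that Statistical methods anticipates. It is not a general bias.

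**What to change.** Put the power statement and Equation (2) on the same outcome and scale, in one of two ways:

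1. Set Y to the natural log of unit cost per client served. Report exp(b3) as a cost ratio with its confidence interval, and keep the arithmetic mean difference as a secondary result for planning. Restate power for this outcome with the DiD estimator and 16 v 15 organisations, giving the SD, correlation and significance level used.
2. If the raw mean difference is to stay primary, restate the detectable difference and power on that scale, with the same inputs shown.

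In either case, remove USD from the log difference and value baseline and endline inputs at one constant price set.

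The cost is wording and one new power calculation; no data collection changes. Under the first option the primary effect becomes a ratio of geometric means, which is less direct for budgeting. Under either option the restated power may be less favourable than 80%.
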